#### Emotion regulation

Emotion regulation will be measured using two emotion reappraisal tasks and the emotion regulation scale. The first emotion regulation task utilises a set of scenarios (different from those use in the emotion regulation training). Participants will be presented with standardised instructions to either look at the scenario and attend to their emotions or reduce their negative affect towards the scenario. There are 24 assessment trials in total split equally between look trials and regulate trials. Self-reported affect recorded after each scenario (using the self-assessment manikin; [62]) will be used to assess emotion regulation success. After completing the assessment task, participants will be provided with one block (four trials) of positively valenced scenarios and asked to attend to the emotions elicited by the scenario. This final, positively valenced block was introduced to avoid inducing persistent negative affect in participants.

In the second emotion regulation task, participants are asked to regulate their emotions in response to images, rather than written scenarios. Images are drawn from the IAPS picture set [76], and have been selected based on those previously been used with developmental populations [77–79]. Participants will be asked to either look at the images and attend to the emotion the image elicits, or reduce the affect they feel in response to the image. This task comprises of four blocks each containing five trials. Two blocks will instruct participants to look at the image and two blocks will instruct participants to reduce their negative affect. After completing the task, participants will be provided with a single block of positive images (5 trials) to avoid inducing persistent negative affect in participants.

Self-report emotion regulation will be assessed using the Emotion Regulation Questionnaire for Children and Adolescents (ERQ-CA; [80]), which is a 10-item scale measuring use of emotion regulation strategies separated into positive emotion regulation strategies (i.e. cognitive reappraisal) and negative emotion regulation strategies (i.e. suppression). For each of the two emotion regulation strategies, scores are summed, with higher values denoting greater use of that emotion regulation strategy.

#### Interoceptive accuracy and attention

Interoception ability will be measured using the Phase Adjustment Task (PAT; [81]), the interoceptive accuracy scale [82] and the interoception attention scale [83]. The PAT involves detecting heartbeats with the device camera and flash. Heartbeat information is used to present tones that are asynchronous with the participant’s heartbeats. Without feeling their pulse, participants must judge synchronicity by adjusting the phase relationship between tones and heartbeats such that tones become synchronous with heartbeats. The starting phase that determines the delay between the tone and participants’ heart beats is randomised across trials [81]. The task begins with 10 ‘screener’ trials in which participants match a tone representing their heartbeat to an asynchronous tone. After completing these practice trials, participants complete 20 assessment trials in which they must match a single tone to their heart rate. To assess performance on the PAT, we will calculate the consistency of selected phase relationships or ‘delays’ across trials [81]. Fifteen trials are required as a minimum to calculate performance on this task. Greater consistency indicates greater interoceptive accuracy whereas more inconsistent responding indicates poorer interoceptive accuracy. Participants with greater consistency are categorised as ‘interoceptive’ whereas participants who are inconsistent are categorised as ‘non-interoceptive’ [81]. In addition to these data, the PAT also records engagement data (e.g. time spent on trials).

Self-report measures of interoception will be collected using the interoceptive awareness and interoceptive attention scales. The interoceptive attention scale measures the extent to which the individual attends to internal signals [83], while the interoceptive accuracy scale measures how adept individuals are at recognising internal bodily signals [82]. Both measures are 21-items, and scores are summed with higher values denoting greater self-reported accuracy or attention (ranging from 21–105).

#### Self-perception

Three questions from the Social Network Analysis of Risky Behaviors in Early Adolescence (SNARE; [84]) will be used to assess the participants’ perception of themselves. The questions are introduced with the stem ‘If you compare yourself with most of your classmates…,’ and participants rate themselves on attributes ‘…how nice are you?,’ ‘…how popular are you?,’ and ‘…how mature are you?’ on a 5-point scale ranging from 1 (‘Much less’) to 5 (‘Much more’).

#### Self-ratings of social relationships

To assess participants’ relationships with those in their social networks, we will measure parent and peer attachments, bullying victimisation and loneliness. Parent and peer attachment will be measured using the inventory of parent and peer attachment (IPPA; [85]). This measure is split into questions regarding relationships with the participant’s mother figure, father figure and close friends. For primary female and male caregivers, there are 28 items assessing parental attachment and for close friends there are 25 items. For each relationship, the scale measures several subdomains including trust, communication and alienation, with higher values denoting more positive attachments. Bullying victimisation will be measured using the multidimensional peer victimisation scale (MPVS; [86]). The scale comprises of 21 items scored on a 5-point response scale. Scores on this scale are summed, with higher values indicating greater victimisation. Finally, loneliness will be measured using the UCLA loneliness scale (version 3; [87]), a 20-item measure of the participant’s isolation from others with higher values denoting greater loneliness.

#### Peer social networks

Network nomination will be used to assess the participants’ friendship networks. Participants will be asked to nominate [88, 89] (i) Who in your year are your best friends? (ii) Who is in your friendship group? (iii) Who are the most popular kids in your year? (iv) Which kids in your year group do you like? Participants can nominate an unlimited number of same-sex and other-sex pupils as they wish for these questions. Two additional questions are also included to assess the effects of intervention: (i) Who gives good advice to you when you are feeling upset? (ii) Who in your year makes others feel accepted/like they belong? In addition, students will also complete the Inclusion of Self Scale (IOS Scale; [90]). This scale asks participants to indicate how close they feel to their peers using Venn diagrams indicating increasingly overlapping circles. Greater overlap indicates the participant feels closer to the nominated peer.

Unlike the other secondary outcome measures, social network data will be collected alongside the screening data from entire year groups in addition to the pre- and post-assessment timepoints with study participants. To construct social networks, we require that the full year group nominate peers for each of the questions to situate study participants within these wider social networks and assess their relations to their peers. The social network data will be completed by year groups in the school term preceding the first group, in Summer 2024 after all groups have run across all study sites, and at a 12-month follow-up in Summer 2025.

### Control variables

#### Backwards digit span

The backwards digit span is a short task measuring working memory capacity [91] and was included as a control variable as it is a measure of general cognitive ability, which may affect the efficacy of the cognitive training [92]. Participants are presented with sequences of numbers and are asked to remember the sequence in reverse order. If participants successfully remember the sequence in reverse order, the number of digits increases by one on the next trial, whereas if participants fail to remember the sequence in reverse order, the number of digits decreases by one on the next trial. The version of the task we use is administered via a tablet as in previous research [93]. Backwards Digit Span data will be collected before the start of the intervention group, immediately after the intervention has been completed and 12 months from the first data collection timepoint for both intervention and control group participants.

### Process evaluation

#### Focus groups and interviews

On completion of the 8-week intervention, a subgroup of participants who took part in the study will be invited to take part in a focus group or 1–1 interviews to discuss their experiences of the group sessions. The focus group and interviews will be facilitated by an independent researcher (i.e. not the group facilitators). Interview and focus group schedules will be semi-structured and will encourage participants to draw on their experience across the full intervention. Participants will be asked about barriers to participation, strategies they found particularly helpful from the sessions, and whether the novel integration of the cognitive-emotional training tasks with psychoeducational content around communication was clear. Questions for the focus group and interviews were developed in collaboration with young people aged 16–17 (*N* = 23), who identified questions that would be important to assess participants’ experience of the intervention, which included features of the group composition and the burden of taking part in the intervention.

#### Stakeholder feedback

In addition to conducting focus groups with adolescents, all stakeholders (intervention group facilitators, head teachers, Special Educational Needs Coordinators and mental health leads) in each site will be invited to complete a survey at the end of the delivery phase. The purpose of this feedback will be to examine facilitators and barriers to delivery and to assess their views on scalability. In addition, we will hold interviews with a subsample of stakeholders to gather qualitative feedback about the delivery of the intervention.

#### Qualitative analysis

Interviews and focus groups with participants and stakeholders will be analysed using framework analysis [94]. This is a qualitative research method involving the research team developing an initial framework based on the core research questions. Each focus group transcript is then thematically analysed in that context to identify core themes. This approach allows the team to draw on both a priori issues (as determined by the interview schedule and topics already identified in the literature) and on themes that emerge inductively from the data.

## Assignment of interventions

### Timing of randomisation

Randomisation will be performed at each school once that school has been provided with a list of participants scoring within the top 25% (i.e. above the cut-off score of 15) of the sample from both year groups. All eligible students will be invited to participate, and students will be randomised in each year group in a numerical order: (a) 1–10 (Group 1)—Term 1, (b) 11–20 (Group 2)—Term 2, and (c) 21–30 (Group 3)—Term 3. As our intervention runs over two academic years in some schools (April 2023–March 2024), some cohorts will transition to the next academic year before the completion of the intervention. For example, the group that is in year 7 when the school is randomised will be in year 8 during the final intervention group run in that school (January–March 2024).

A random selection of eligible adolescents will subsequently be invited to participate in the main study. Parents will receive consent forms detailing the aims of the study, the structure of the intervention and the time commitment expected of participants (see Additional file 1: Appendix), which will also include a consent form. Once parental consent has been obtained, participants will be randomly allocated to one of the three school terms (i.e. the sample will be split into thirds with one third taking part in term 1, a second third taking part in term 2, and the final third taking part in term 3). At the beginning of the allocated term, consent will be sought from the young person, and they will complete the assessment battery comprising of mental health, emotion processing and social relationship measures (see Fig. 4). Participants allocated to the intervention arm of the study will then complete 10 sessions inclusive of individual pre-group sessions, 8 weekly group sessions, and a mid-group session. Participants allocated to the control arm of the study will complete their usual classroom schedule.

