**Fig. 4 Fig4:**

Schematic of the project timeline

Procedures are also in place to account for drop-out of participants. Should any young people drop out before the intervention has begun (prior to the one-to-one meeting with the group facilitator), the next consecutive student in the list will be invited to take their place (i.e. student 31, student 32, etc.) and baseline assessments will be conducted. On the other hand, any students who ‘drop-out’ between baseline assessment and intervention will be treated as ‘intention to treat’ and therefore will be invited to take part in the follow-up assessment even if they do not participate in the ReSET group.

For the integrity of the randomisation to be preserved, it is crucial that the allocation of young people to a treatment within a given school occurs *after* all eligible children from that school (and their parents) have been screened and consented to take part. If a child or a parent knew, at the point of baseline assessment and/or at the point of making the decision whether to take part, which treatment arm they would be signing up for, then participation would not be independent of randomisation. This would risk selection effects which have the potential to cause bias in the estimation of intervention effects. As such, we will screen the entirety of the participating year groups at the first screening timepoint, and students will only be informed which group they have been allocated to only after they have completed their baseline assessment. We expect modest increases in symptomology between the screening phase and the beginning of the third set of assessments in line with population-level changes to psychopathology during adolescence (e.g. [95]). However, it is vital to the randomisation procedure that participants and their parents consent to take part in the study *prior* to when randomisation takes place, which necessitates that we screen and consent participants in the top 25% of SDQ scores at a single timepoint. We will collect SDQ data at our baseline assessment in addition to this screening questionnaire, which will allow us to adjust for changes to general psychopathology between the first screening timepoint and when the participant completes the baseline assessment.

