### Randomisation schedule

Randomisation will be carried out in randomly permuted blocks of size 2. Each block has two elements:Cohort1-INT: Year 7 cohort receives the intervention, Year 8 cohort is the control groupCohort2-INT: Year 7 cohort is the control group, Year 8 cohort receives the intervention

A statistical programme to generate a randomised list of permuted blocks will be written by the project statistician, PM, using the R Software for Statistical Computing. This programme will then be used by an independent statistician not involved in the study to generate a randomised list. The independent statistician will use a new seed number to generate the list, and pass this on to the trial manager, LL. The trial manager will use the list to allocate year groups to treatment arms, going down the list in the order in which schools are ready to be randomised (see Additional file 1: Appendix for R script).

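### The protocol gives two incompatible orders for consent and randomisation, and pupils in later terms consent and complete baseline after their school is randomised on either reading

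*Protocol article*

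**What the plan says.** All of this stands in the Protocol article under Assignment of interventions.

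The opening paragraphs of Timing of randomisation describe these steps:

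- The trigger for allocation is the screening list: "Randomisation will be performed at each school once that school has been provided with a list of participants scoring within the top 25" per cent. Consent is not named as a condition.
- Invitation is placed later: "A random selection of eligible adolescents will subsequently be invited to participate in the main study".
- Parental consent comes next, and the randomisation that follows it is to a term, not an arm: "Once parental consent has been obtained, participants will be randomly allocated to one of the three school terms".
- The pupil's own consent and the baseline come last: "At the beginning of the allocated term, consent will be sought from the young person, and they will complete the assessment battery".

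The text after Fig. 4 calls it crucial that allocation within a school comes after "all eligible children from that school (and their parents) have been screened and consented to take part". It repeats the requirement as vital, and explains that knowing the arm when deciding to take part, or at baseline, could bias the estimated effect. It adds one safeguard: "students will only be informed which group they have been allocated to only after they have completed their baseline assessment". It also lets the next pupil on the list replace anyone who leaves before the one-to-one meeting.

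Under Randomisation schedule the unit is the whole year group: "The trial manager will use the list to allocate year groups to treatment arms", taking schools in the order in which they become ready.

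**The concern.** The protocol makes the integrity of its randomisation depend on consent coming first, and then describes a procedure in which it comes second. A team that follows the opening paragraphs would recruit into year groups whose arm is already fixed. Families' decisions to join, school judgements about who is unsuitable for a group, and the self-reported baseline could then all depend on the arm. This is the recruitment and identification bias familiar from cluster trials.

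The primary model adjusts for the baseline score of the outcome. That adjustment does not remove selection on unmeasured factors, and it is weakened if the baseline itself was answered in knowledge of the arm.

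**Working it through.** No figure in the plan decides this point. The check is a comparison of the two sequences, followed by a count of the pupils affected.

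**1. What randomisation refers to in the opening paragraphs.** The paragraphs also speak of pupils being randomised in numerical order to terms, so the word could be misread. But the trigger is stated per school, and the same paragraphs later refer to the year a cohort is in when its school is randomised. The trigger therefore concerns allocation of the school's year groups to arms.

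**2. The two orders.**

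- Opening paragraphs: screening list, school randomised, invitation, parental consent, allocation to a term, pupil consent and baseline at the start of that term.
- After Fig. 4: screening, consent of pupils and parents at a single time point, school randomised, baseline, disclosure of the arm.

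In the first, every consent follows randomisation. In the second, every consent precedes it.

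**3. The most favourable reading.** Suppose parental consent in fact comes before allocation. The school is still randomised once, while pupil consent is spread over up to three terms. Pupils of the second and third terms then consent after randomisation, which the text after Fig. 4 rules out. The same holds for replacements, who are invited only when someone ahead of them has left. The consent meant after Fig. 4 cannot be the parental opt-out for screening in Timeline, because it is described as agreement by participants and parents to take part in the study.

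**4. Whether the arm can stay hidden.** One year group is entirely intervention and the other entirely control (Trial design, Randomisation schedule). Groups meet in a classroom of the pupils' own school (Study setting), and class teachers release pupils to attend (Adherence). Once Term 1 groups have run, the arm of that year group may be visible to pupils who have yet to consent and complete baseline.

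**5. How many pupils.** Inputs: 540 pupils, nine schools, 27 groups of 10 (Sample size calculation); two or three terms per school (Timeline).

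- Three terms everywhere: 540 / 3 = 180 per term; 2 × 180 = 360, or two thirds.
- Two terms in a school: one of two terms is later, so half of its pupils.
- The plan's fallback of two schools with two groups each: 7 × 3 + 2 × 2 = 25 groups, of which 7 × 2 + 2 × 1 = 16 are later. 16 / 25 = 64%, or 320 of 500 pupils if controls follow the same timetable.

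Each is an upper limit, because not every later pupil need become aware.

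**6. What an undetected bias would do, for scale only.** The plan's stated power is 92.8%. With 216 analysed per arm, 8 per group, 24 per year group, ICCs of 0.05 and 0.02 and baseline correlation 0.5, a normal approximation gives:

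- Intervention variance: 0.75 × (1 + 7 × 0.05 + 23 × 0.02) / 216 = 0.75 × 1.81 / 216 = 0.00628
- Control variance: 0.75 × (1 + 23 × 0.02) / 216 = 0.75 × 1.46 / 216 = 0.00507
- SE = √0.01135 = 0.1066; power = Φ(0.4 / 0.1066 − 2.2414) = 93.5%, close to the plan's figure.

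With that SE, an arm difference b left after adjustment makes the two-sided type I error 1 − Φ(2.2414 − b/SE) + Φ(−2.2414 − b/SE). For assumed b of 0.05, 0.10 and 0.20 SD (0.18, 0.36 and 0.72 SDQ points at SD 3.6) it is about 4.2%, 9.7% and 35.8%, against a nominal 2.5%. These values of b are assumptions, not estimates.

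**The case against.** The best defence is that the opening paragraphs are loosely drafted, not a deliberate choice to randomise first. They are not strictly chronological: they say that all eligible pupils are invited and then that a random selection is. Supplying the list may be a necessary condition only, and the later invitation may mean later than screening. The text after Fig. 4 gives the rule twice, with its reason, and could be taken as governing. This is fair as to intent, and a reader should not infer that the trial chose a biased design. It does not settle the order, and it leaves the later-term consents where they were.

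Three stronger readings are tempting but not supported:

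- **That later pupils will know their arm.** The document does not say so. Groups hold up to 10 pupils in a year of about 240, disclosure is promised only after baseline, and Blinding limits who knows the allocation. Visibility is a possibility.
- **That blocks of two make the allocation usefully predictable.** With nine schools, 4 of 9 allocations follow from the previous one. But every school contains both arms, so prediction cannot steer pupils between schools. Harm would require uneven recruitment of the two year groups within a school, and nothing says that the school staff who send consent forms hold the list.
- **That a definite bias can be stated.** Multiplying an assumed share of arm-driven decisions by an assumed outcome difference yields a number, but neither input is in the document.

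A partial safeguard also deserves credit. The SDQ is collected from whole year groups at screening, before randomisation on either reading.

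**Conclusion.** The contradiction is established from the text and depends on no assumption: one section gives two orders of consent and randomisation, and the protocol itself says that the integrity of randomisation rests on which is followed. The most favourable reading still leaves pupil consent and baseline after randomisation for later terms and replacements.

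The exposure is at most about 360 of 540 pupils if every school uses three terms, and half the pupils of any school that uses two. The consequence is that selection bias is permitted, not that it has been shown. Its size cannot be derived from the document. The passages must be reconciled.

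**What to change.** Rewrite Timing of randomisation as one sequence for each school:

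1. Apply the school's exclusions to both year groups.
2. Obtain parental consent and the young person's assent for invited pupils and reserves, in both year groups and for all terms. Reconfirm assent at the start of the term. State whether all eligible pupils or a random selection are invited.
3. Lock the ordered list, reserves included.
4. Only then release that school's allocation, preferably one school at a time by the independent statistician.

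Define the intention-to-treat set as the pupils called from the locked list who were enrolled. Reserves who were never called do not belong in it. Clarify the replacement rule at the same time: a pupil who leaves after baseline but before the one-to-one meeting now falls under both the replacement rule and the intention-to-treat rule.

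Earlier assent does not protect the later-term baselines, which still follow the Term 1 groups. Use the screening SDQ to compare those who joined by arm and term, and as a covariate in a sensitivity analysis of the SDQ outcome. Timeline lists no wellbeing scale at screening, so this does not extend to the second primary outcome.

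Trial status gives recruitment from 09/03/2023 to about 31/03/2024. Where schools are already randomised, document the order actually used in each and report consent rates and baseline by arm and term.

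The cost is earlier assent and a little more school administration. Sample size and the primary model are unchanged.

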### Timeline

Schools will be recruited in the academic year prior to the start of the intervention (i.e. for schools participating in April 2023–July 2024, we will recruit schools from September 2022–September 2023). We intend for each participating school to run a minimum of two intervention groups across two school terms and a maximum of three intervention groups across three school terms. Once schools have been recruited, consent forms will be sent to parents/carers of the participating year group cohorts asking them to indicate if they would not like their child to complete the screening measures (i.e. we will utilise an opt-out procedure). Once the deadline for returning consent forms has passed, participating adolescents will complete the SDQ, Me and My Feelings Questionnaire, and Peer Social Network nominations. We will then invite students who report SDQ total difficulties scores of 15 or higher—corresponding to the top 25% nationally, as estimated based on recent national data [51].

After the conclusion of the intervention, participants from both the intervention and control arms of the study will complete the assessment tasks measuring mental health, emotion processing and social relationship detailed in the “Outcomes” section. Once all three groups have been run within a school, we will collect follow-up measures consisting of the SDQ, M&MF and peer nomination to allow us to estimate social networks within the year group. SDQ, M&MF and peer nomination data will be collected from all students in the year group (not just those eligible to take part in the groups). Finally, 1 year following the completion of the intervention, participants from the intervention and control arms of the study will complete the full battery of assessments tasks as well as the social network measures (see Fig. 5).

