*Mental Wellbeing* will be assessed by the WEMWBS. There are few published data sets allowing estimation of the distribution of this scale among younger teenagers, and none for our specific at-risk population (top 25% in mental health problems). As the closest available approximation, we used data from the 2018 sweep of the Millennium Cohort Study (MCS), when cohort members were 17 years old. This was the only study we found that measured both SDQ and WEMWBS for the same participants. In contrast to our own study, the MCS used the short (7-item) version of the well-being scale, the SWEMWBS. Selecting the 25% participants with the highest SDQ total difficulties score (SDQ ≥ 15, *n* = 2473) gave us an estimate of SD = 4.7 for the SWEMWBS. We decided to assume the slightly larger SD = 5 for the calculations below, for simplicity and to err on the conservative side. It is not clear what size of points difference on the SWEMWBS is clinically meaningful or subjectively important to children, although change scores as small as either 1 or 3 points have been cited as minimally important change on the individual level [100]. Raw effect sizes of 1, 2 and 3 points would correspond to standardised effect sizes of about 0.2, 0.4 and 0.6. Since there is a high correlation between the 7-item SWEMWBS and the 14-item WEMWBS, we assume that these results will scale appropriately to the longer version of the scale, which we will use in our study.

The aim of the power analysis was to determine the number of schools that need to be recruited to give us 90% power to detect a moderate effect of the intervention (δ = 0.4) for each of the SDQ Total Difficulties Score and the WEMWBS. To correct for multiple testing of our two primary outcomes, we set alpha at 0.025 for a two-sided test. We will select larger than average schools such that each school year will have around 240 pupils or more. With 25% of pupils meeting the entry threshold, and estimating that 50% agree to take part, we considered that we are likely to recruit 30 students per school year, and thus 60 students per school. The group intervention was assumed to be delivered in groups of 10. Thus, we expect to run approximately three intervention groups per school.

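### The protocol invites all eligible pupils in one paragraph and a random selection in the next, so it is unclear whether the numbered list and its reserves hold pupils who have already consented

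*Protocol article*

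**What the plan says.** All references are to the protocol article.

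- **Timing of randomisation, first paragraph:** "All eligible students will be invited to participate, and students will be randomised in each year group in a numerical order". Places 1–10, 11–20 and 21–30 are tied to Terms 1, 2 and 3. Consent is not mentioned.
- **Same section, second paragraph:** "A random selection of eligible adolescents will subsequently be invited to participate in the main study". Parental consent forms are described after this. Then: "Once parental consent has been obtained, participants will be randomly allocated to one of the three school terms", and "At the beginning of the allocated term, consent will be sought from the young person".
- **Same section, after Fig. 4:** if a pupil drops out before the first individual meeting, "the next consecutive student in the list will be invited to take their place", with students 31 and 32 as examples. The next paragraph calls it crucial that arm allocation in a school follows the point at which "all eligible children from that school (and their parents) have been screened and consented to take part".
- **Timeline:** "We will then invite students who report SDQ total difficulties scores of 15 or higher". No sub-sampling is mentioned.
- **Preliminary considerations (sample size):** year groups of around 240 pupils or more, and "With 25% of pupils meeting the entry threshold, and estimating that 50% agree to take part", giving 30 recruits per year group and 60 per school. The total is 540 from nine schools.

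**The concern.** The two invitation rules cannot both be followed. They differ on who is approached, and they leave open what the numbered list contains: eligible pupils not yet asked, or pupils whose parents have agreed.

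That matters most for replacements. Arm is set for a whole year group, and intervention groups run in successive terms. If students 31, 32 and so on consented before the arm was set, calling them up is harmless. If they are first invited when a place falls vacant, their decision to join comes after allocation. The protocol itself warns that participation would then not be independent of randomisation and that the estimated effect could be biased.

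A second consequence is yield. The recruitment forecast fits only one of the two rules as written.

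**Working it through.** **1. The passages side by side.** Inviting all fits the first paragraph of Timing of randomisation, the Timeline, the requirement that all eligible children and parents consent before allocation, and the recruitment forecast. A random selection fits the second paragraph. It also fits the replacement rule, where the next student on the list is still to be invited. Numbering before consent is implied by the order of the two paragraphs and by the replacement rule; it is not stated outright. Random allocation to term after parental consent is stated.

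**2. The plan's own recruitment figure.** Inputs: 240 pupils per year group, 25% eligible, 50% uptake, two year groups in each of nine schools (18 year groups).

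- Eligible per year group: 240 x 0.25 = 60.
- Recruits per year group: 60 x 0.5 = 30.
- Total: 30 x 18 = 540.

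This matches the protocol exactly. The share of eligible pupils invited, *f*, does not appear, so it is implicitly 1.

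**3. The same inputs with *f* below 1.** The protocol gives no value for *f*, so the values below are assumptions. Total = 540 x *f*; uptake needed for 30 recruits = 30 / (60 x *f*); year-group size needed = 30 / (0.25 x 0.5 x *f*).

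| *f* | Recruits | Uptake needed at 240 pupils | Year-group size needed at 50% uptake |
|---|---|---|---|
| 1 | 540 | 50% | 240 |
| 0.9 | 486 | 56% | 267 |
| 0.75 | 405 | 67% | 320 |
| 0.5 | 270 | 100% | 480 |

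**4. Slack in the inputs.** The 240 is roughly a floor. In the reference survey 604/2100 = 28.8% scored at or above the cut-off. At that share, 240 x 0.288 x 0.5 = 34.5 recruits per year group, so *f* of about 30/34.5 = 0.87 would still give 30.

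**5. Power.** Inputs: effect 0.4, two-sided alpha 0.025 (z = 2.241), group ICC 0.05, year ICC 0.02, baseline correlation 0.5 (variance factor 1 − 0.25 = 0.75), 20% loss. That leaves 216 analysed per arm, 8 per group and 24 per year group.

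- Additive design effects: intervention 1 + 7(0.05) + 23(0.02) = 1.81; control 1 + 23(0.02) = 1.46.
- SE² = 0.75 x (1.81 + 1.46)/216 = 0.01135, so SE = 0.1066.
- 0.4/0.1066 − 2.241 = 1.51, giving power of 93.5%.
- With a product design effect in the intervention arm (1.35 x 1.46 = 1.97), power is 92.3%.

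The protocol states 92.8%. For 25 groups and 250 controls the two forms give 92.1% and 90.8%, against 90.5% stated. Agreement is within two points.

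If recruitment falls in proportion to *f*, with group size kept at 10 and year-group size falling, power (additive / product) is 91.5% / 90.2% at 486, 87.2% / 85.8% at 405 and 73.6% / 72.4% at 270.

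**The case against.** The strongest reply is that one sentence is out of line and the rest of the protocol settles the matter: the Timeline, the consent requirement and the forecast all point to inviting everyone. The stray sentence may only mean that places are filled at random where numbers exceed capacity, since groups are capped at 10 and schools at three groups. This is plausible, but the sentence selects from eligible adolescents, and the parental forms come after it. It does not say that consenting pupils are selected.

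Three stronger readings are tempting and are not supported:

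- **That only inviting everyone can yield 540.** Larger year groups or the survey's 28.8% share leave room for a mild selection. A shortfall to 486 still keeps about 90% power.
- **That recruitment would halve to 270, with about five pupils per term group.** No passage sets the selection at 30 pupils. The figure of five comes from joining the first paragraph's blocks to the second paragraph's invitation rule and ignoring replacement. In the table above, 270 is only the illustrative case of *f* = 0.5.
- **That late entrants join knowing their arm.** The protocol says that pupils learn their allocation only after baseline assessment. A later invitee might infer the arm from groups already run in the same year group, but that is an inference and the documents do not show it.

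It is also fair that, if one rule is applied alike to both year groups, the selection is the same in both arms and does not in itself bias the comparison.

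It could further be said that any replacement risk belongs to the replacement rule alone. That does not stand: the rule is safe if student 31 has already consented and unsafe if not, and the contradictory invitation rules are what leave this open.

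**Conclusion.** The contradiction is real and should be corrected. The protocol gives two invitation rules and two accounts of term order, and it does not say whether the numbered list and its reserves hold consented pupils.

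The 540 target contains no sampling fraction and so assumes that all eligible pupils are invited. At the planning values any selection falls short: 486, 405 or 270 for 90%, 75% or 50% invited. These totals rest on assumed shares and on exactly 240 pupils, 25% eligible and 50% uptake.

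The main reason to act is the order of consent and allocation for replacements. Under the random-selection reading, pupils from 31 on would first be invited after the arm is set, contrary to a safeguard the protocol calls crucial. Whether this happened, and whether it biased anything, cannot be judged from the document. The power formula and the allocation by year group are not affected.

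**What to change.** Delete the sentence on inviting a random selection, and state one sequence for both arms:

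1. Invite every eligible pupil in both year groups once.
2. Obtain parental consent.
3. Put the consenting pupils of each year group in one random order.
4. Give numbers 1–10, 11–20 and 21–30 Terms 1, 2 and 3.
5. Draw replacements, in order, only from already-consented pupils from 31 on. Amend the replacement rule after Fig. 4 so that these pupils are called up and not newly invited.

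Because the young person's own consent is sought at the start of the allocated term, the text should also say how that step fits the requirement that children as well as parents consent before allocation.

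The cost is wording, with two practical downsides. At the planning values about 30 pupils consent per year group, so the reserve may be small or empty. Where more consent, some families may agree and not be offered a place.

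The Trial status section gives recruitment as running from 09/03/2023 to about 31/03/2024. If it is complete, do not rewrite the rule after the event. State which rule each school used, and whether any replacement was invited after the year group's arm was set.
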